**Methods:**

The REQUEST (Remote Monitoring by viQtor Upon Implementation on a Surgical Department) study is a prospective observational implementation study conducted over 8 months in a surgical ward. The vital signs of 500 postoperative patients will be continuously monitored using the viQtor device, which measures heart rate, respiratory rate, and oxygen saturation. The study consists of 2 phases: an initial period with manual spot checks, followed by a phase using the wearable device as the primary monitoring tool. Outcomes include the Integrated Workload Scale for nursing workload and a framework evaluating acceptability, feasibility, adoption, and sustainability. Data collection involves device performance metrics, questionnaires (the Evidence-Based Practice Attitude Scale and the System Usability Scale), and thematic analysis of focus groups.

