## Introduction

The health care sector is currently undergoing a significant transformation, with increasing emphasis on integrating smart technologies to enhance patient safety and clinical efficiency. A central innovation in this shift is the use of wearable monitoring devices in hospitals, particularly for patients recovering from major abdominal surgery. These procedures are associated with a high risk of serious adverse events, which could lead to preventable harm if early signs of clinical deterioration—often evident in vital sign changes—go unnoticed [1].

Current early warning systems are based on intermittent manual assessments of vital signs, and the Early Warning Score (EWS), typically performed three times daily. However, research indicates that deterioration in vital parameters often precedes clinical events by several hours. One study found that in approximately 60% of patients who experienced postoperative complications, changes in vital signs had already occurred but were not recognized in time due to the limited frequency of monitoring [2].

Efforts have been made to improve the EWS, such as the development of the Modified Early Warning Score (MEWS), which incorporates oxygen saturation [3,4]. While these adaptations have increased the sophistication of monitoring, the overall predictive value of these systems remains limited [2,5]. Moreover, variation in EWS methodologies and inconsistent validation have raised concerns about reliability in daily clinical practice [6].

Advancements in wearable technology offer a promising alternative. These devices provide real-time, continuous monitoring of vital signs, enabling earlier detection of clinical deterioration and potentially more timely intervention [4,7-9]. In addition, continuous monitoring may reduce the burden of manual assessments on nursing staff. Despite the potential benefits, widespread implementation of wearables in clinical settings remains uncommon. Most studies to date have focused on technical performance, while few have explored how such devices are adopted and integrated into routine care.

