## Methods

### Setting

This prospective implementation study with retrospective data analysis (the REQUEST [Remote Monitoring by viQtor Upon Implementation on a Surgical Department] trial) will be conducted at a large teaching hospital. All adult patients (aged 18 years and older) admitted to the surgical department for elective procedures will be eligible for inclusion, provided they meet our inclusion criteria and provide informed consent. Patients unable to wear the device or unwilling to participate will be excluded.

The viQtor device, developed by SMARTCARE, was selected due to its proven capability for autonomous, continuous monitoring and its established structure for seamless data transfer into the electronic health record (EHR). The device is CE (Conformité Européenne)-certified and transmits data every minute via a cellular network without the need for any hub. Each vital sign—heart rate, respiratory rate, and peripheral oxygen saturation (SpO₂)—is updated every minute, with data being transferred to the EHR. The device provides median values from the last 4 hours for each vital sign, which means that the system aggregates data over that period to ensure stability in measurements. In the event of missing data, the system generates flags to indicate the absence of readings, and data imputation strategies will be applied. By using clinical-grade photoplethysmography sensor technology, the device allows accurate tracking of heart rate, respiratory rate, and SpO₂. Although the device can also measure skin temperature, this parameter will not be used in this study.
The solution comprises a device with a charger and an armband. The device is worn on the upper arm under clothing and is applied upon admission (Figure 1).

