### Implementation Phase

Implementation of the device as the new standard of care for monitoring will be executed in 2 distinct phases to ensure a thorough evaluation and implementation of this monitoring system (Table 1).

During phase 1 (the initial phase; months 1-3), patients will continue to receive the current standard of care, which involves manual spot checks and MEWS measurements by nursing staff. Concurrently, all health care staff will receive training on the application, data interpretation, and protocol adherence concerning the solution to optimize the infrastructure before its implementation.

Following phase 1 (in month 4; the evaluation and validation period), the preimplementation phase will be evaluated. Predictive accuracy will be evaluated by comparing device data against clinical outcomes such as complications, intensive care unit transfers, or MEWS-triggered interventions using area under the receiver operating characteristic curve analysis.

In phase 2 (months 5-8), the wearable will become the primary tool for patient monitoring, supplemented by manual spot checks by nurses as needed. This phase aims to evaluate the integration into standard care.

During the whole study, every minute data are securely stored. During phase 2 of the study, 6 times a day, median values of the previous 4-hour window will be uploaded to the EHR. In case of signal loss or low-quality readings, the system generates flags, allowing for assessment of signal-to-noise ratio (SNR).

**Table 1 table1:** Psychometric properties and statistical analysis.

Objective	Instrument	Variable	Statistical test	Achievement criteria
Fidelity	SUS^a^	Continuous	Unpaired *t* test or Mann-Whitney *U* test	Fidelity achieved when protocol adherence is ≥95%
Acceptance	SC^b^/day	Continuous	Descriptive statistics	Acceptance achieved when ≥75% of nurses use the device regularly
Acceptance	SC/patient	Continuous	Descriptive statistics	Acceptance achieved when ≥75% of nurses use the device regularly
Acceptance	IWS^c^	Ordinal	1-way ANOVA	Acceptance achieved when ≥75% of nurses use the device regularly
Adoption	EBPAS^d^	Continuous	Repeated measures ANOVA	Adoption achieved when device use exceeds 70% by clinical staff
Appropriateness	SNR^e^	Continuous	Descriptive statistics	Adoption achieved when device use exceeds 70% by clinical staff
Appropriateness	ADE^f^	Continuous	Descriptive statistics	Appropriateness achieved with minimal ADEs

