Feasibility	Thematic analysis	Nominal	Braun and Clarke [11] thematic analysis	Feasibility achieved when 80% of clinicians can successfully implement the device
Time efficiency	Time measurement	Continuous	Descriptive statistics	Time efficiency achieved when nurses’ time spent on monitoring decreases by ≥20%
Predictive accuracy	MEWS^g^ and CREWS^h^	Nominal	AUROC^i^	Predictive accuracy achieved when AUROC ≥0.80

^a^SUS: System Usability Scale.

^b^SC: spot check.

^c^IWS: Integrated Workload Scale.

^d^EBPAS: Evidence Based Practice Attitude Scale.

^e^SNR: signal-to-noise ratio.

^f^ADE: adverse device event.

^g^MEWS: Modified Early Warning Score.

^h^CREWS: Continuous Remote Early Warning Score.

^i^AUROC: area under the receiver operating characteristic curve.

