### Outcomes

The primary objective of this study is to evaluate the implementation of a new wearable on the surgical ward at Catharina Hospital Eindhoven. This will be achieved by assessing its usability, degree of implementation, and the workload for nursing staff. The primary outcome will be acceptability, specifically evaluating workload as measured by the Integrated Workload Scale (IWS). The IWS is a comprehensive tool that provides multidimensional descriptions and gradations of workload, ranging from “not demanding” to “work too demanding” on a 9-point Likert scale. This scale is suitable for both periodic assessment and real-time monitoring of tasks, with measurements conducted throughout the entire study period.

For secondary outcomes, the study will apply the framework of the taxonomy of implementation outcomes of Proctor et al [12], focusing on adoption, feasibility, appropriateness, predictive accuracy, and technical feasibility. Adoption will be measured by the Evidence-Based Practice Attitude Scale and the System Usability Scale, along with the amount of spot checks conducted in addition to the standard monitoring.

Feasibility will be evaluated by determining the extent to which health care employees can successfully implement the device, and by measuring the time required to perform and process manual spot checks or digital monitoring checks. Appropriateness will be assessed by examining the SNR and counting the number of (suspected) adverse events that occur during or result from the use of the wearable.

Additionally, the predictive accuracy for early detection of health deterioration and postoperative complications among patients will be evaluated through focus group discussions. Technical feasibility will involve analyzing the availability of data on the web platform, including monitoring time and the types and quantities of algorithm artifacts, such as low-quality data during the monitoring of photoplethysmography values.

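### MEWS-triggered interventions are listed as a reference outcome for the predictive-accuracy AUROC, which is circular for MEWS and turns the device score's AUROC partly into a measure of agreement with MEWS

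*Protocol article*

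**What the plan says.** Methods, Implementation Phase, describes the month 4 evaluation of phase 1. Predictive accuracy is to be assessed with AUROC by "comparing device data against clinical outcomes such as complications, intensive care unit transfers, or MEWS-triggered interventions". The Predictive accuracy row of Table 1, in the same section, names MEWS and CREWS as the instruments and AUROC as the test. Its success criterion is "Predictive accuracy achieved when AUROC ≥0.80". The row does not say which score or which outcome the criterion applies to.

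In phase 1 the standard of care is "manual spot checks and MEWS measurements by nursing staff". MEWS therefore guides care in the months that the month 4 evaluation looks back on.

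On the overlap between the scores, Setting says of the device: "Each vital sign—heart rate, respiratory rate, and peripheral oxygen saturation (SpO₂)—is updated every minute". The Introduction describes the "Modified Early Warning Score (MEWS), which incorporates oxygen saturation". The other components of MEWS, and all components of CREWS, are not listed.

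The Outcomes section places predictive accuracy among the secondary outcomes and gives a different method: "the predictive accuracy for early detection of health deterioration and postoperative complications among patients will be evaluated through focus group discussions".

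**The concern.** A reference outcome for an AUROC should be ascertained independently of the score under test. A MEWS-triggered intervention is not independent of MEWS, because it occurs when MEWS is high. Counting it as an event credits MEWS with predicting its own consequence. This is incorporation bias, and for MEWS it acts upward.

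For the device score the problem is different. In phase 1 the trigger is the nurse-measured score, so an AUROC for device data against triggered interventions asks partly whether the device agrees with the nurses' MEWS. That is a legitimate question, but it is not prediction of deterioration.

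Two conclusions are at stake. MEWS could pass 0.80 with a clearly lower AUROC for independent outcomes. And if the two scores are read side by side on this outcome, MEWS has a built-in advantage, which is unhelpful in a study meant to learn what the device adds.

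**Working it through.** **What can be reproduced.** The 0.80 is a criterion, not a derived figure. The document gives no expected AUROC, event rate, MEWS trigger level or correlation between the scores. Everything below rests on assumed inputs and shows how the bias behaves, not its size in this trial. CREWS is taken to be the score built on device data.

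**Step 1: mixture identity for MEWS.** Suppose triggered interventions are pooled with independent outcomes. Let w be the share of events that are MEWS-triggered only. Let A0 be the AUROC for independent outcomes and A1 the AUROC for triggered-only events, both against the non-events of the pooled outcome. Then

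AUROC(pooled) = (1 − w) × A0 + w × A1.

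If MEWS separates its own triggered events perfectly, A1 = 1, and 0.80 is reached at w = (0.80 − A0) / (1 − A0):

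- A0 = 0.60: 0.20 / 0.40 = 50%
- A0 = 0.65: 0.15 / 0.35 = 43%
- A0 = 0.70: 0.10 / 0.30 = 33%
- A0 = 0.75: 0.05 / 0.25 = 20%

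Pooling also removes patients with high MEWS from the non-events, which raises A0 itself. Measured from the AUROC against all patients without an independent outcome, the share needed is therefore somewhat smaller. In a simulation with 10% independent outcomes and the top 5% of MEWS triggering, w was 0.26 and MEWS went from 0.70 to 0.796. The identity with A0 = 0.70 gives only 0.74 × 0.70 + 0.26 = 0.778.

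**Step 2: both scores by simulation.** Assumptions: 15% of patients have a complication or ICU transfer. Each score is normal with unit variance, shifted by √2 × Φ⁻¹(0.70) = 0.742 in patients with the outcome, so each has AUROC 0.70. The top 10% of MEWS values trigger an intervention. The pooled event is outcome or trigger. Correlation is within outcome group.

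| Score | Correlation with MEWS | Independent outcomes | Pooled outcome |
|---|---|---|---|
| MEWS | – | 0.70 | 0.82 |
| CREWS | 0 | 0.70 | 0.64 |
| CREWS | 0.3 | 0.70 | 0.70 |
| CREWS | 0.5 | 0.70 | 0.74 |
| CREWS | 0.7 | 0.70 | 0.78 |

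I reran this with 1,000,000 patients per scenario and obtained the same values to within rounding.

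**Step 3: sensitivity.**

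- Starting from 0.75: MEWS 0.85; CREWS 0.77 at correlation 0.5 and 0.81 at 0.7.
- Top 5% triggering: MEWS goes from 0.70 to 0.77 and from 0.75 to 0.80.
- 10% independent outcomes, top 3–10% triggering, intervention given in 50–100% of triggers, starting from 0.70: MEWS 0.73–0.86; CREWS 0.61–0.68 at correlation 0, 0.71–0.75 at 0.5, 0.72–0.80 at 0.7 and 0.73–0.84 at 0.9.

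**Step 4: triggered interventions as the only endpoint.** The list of outcomes permits this. MEWS then scores 1.00 if every trigger leads to an intervention, and 0.97–0.99 if half do. A CREWS with AUROC 0.70 for independent outcomes scores 0.79–0.82 at correlation 0.5 and 0.88–0.91 at 0.7 (top 5–10% triggering, every trigger acted on).

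**The case against.** The strongest reply is that the sentence on the month 4 evaluation tests device data, not MEWS. A reader might infer that the evaluated device score defines its own events. The document does not support that: nurse-measured MEWS is the phase 1 standard, and the upload of device medians to the health record is described for phase 2. This stands, and for the device the issue is correlated measurement rather than incorporation bias. It does not clear MEWS, which Table 1 places under the same AUROC criterion.

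Second, the outcomes are examples in an open list, and no composite is stated. Separate AUROCs per outcome would fit the text, and those for complications and ICU transfer would then not be defined by MEWS. This stands too, and it is why the size cannot be fixed. But triggered interventions are named as an acceptable outcome, and analysed alone they are the worst case.

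Third, a reader might infer that the device's AUROC is bound to be inflated, or that a device without predictive value would pass. Neither follows. The direction depends on agreement with MEWS, and of the four main CREWS scenarios (0.70 or 0.75, correlation 0.5 or 0.7) only one crosses 0.80, starting from 0.75. The shared inputs are also only partly documented: oxygen saturation is the one component that the document names for both MEWS and the device.

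Fourth, no test of MEWS against CREWS is stated, so the advantage to MEWS concerns how the results may be read, not a planned analysis.

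Finally, predictive accuracy is secondary, and no passage makes the 0.80 criterion a gate for phase 2. That lowers the severity but does not remove the point: the text names an unsuitable outcome beside a numerical pass mark, so this is not merely detail left to a fuller document.

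**Conclusion.** The point holds in a limited form. For MEWS the reference outcome is circular wherever triggered interventions are counted, and the estimated AUROC is biased upward. It is the estimate that is distorted; the 0.80 target is a fixed number. For the device score, the AUROC partly reflects agreement with nurse-measured MEWS and may rise, stay the same or fall.

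In the main scenario the shift is +0.12 for MEWS (0.82 − 0.70) and between −0.06 and +0.08 for CREWS over correlations of 0 to 0.7. These figures rest on the assumed event rate, trigger share, correlation and binormal scores, and on pooling the outcomes. The trial's own figure cannot be derived from the document. Severity is moderate.

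**What to change.** In Implementation Phase, remove MEWS-triggered interventions from the AUROC reference outcome. Use complications and ICU transfers, classified without reference to MEWS or CREWS values. Report MEWS-triggered interventions separately, as a descriptive process measure or as an analysis of agreement between the device and MEWS. In Table 1, state which score and which outcome the 0.80 criterion applies to. Reconcile this with the sentence in Outcomes that assigns predictive accuracy to focus groups, since the edit alone would leave two methods for one objective.

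The cost is small: a sentence and a table entry, with no change to data collection. There are two drawbacks. Fewer events mean a wider confidence interval. And a patient whose triggered intervention averted a complication or ICU transfer will count as a non-event, which penalises a score that flagged that patient correctly; this should be stated as a limitation.

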Approximately 70 nurses from the surgical ward will participate in the study and complete the IWS. In addition, 10 nurses and 5 physicians will voluntarily join focus groups to conduct an in-depth evaluation of the new implementation. These focus groups, which will be established prior to the study’s commencement, will meet 3 times during the study period to discuss the progress of the study and share their experiences with the implementation. A structured analysis of fidelity, feasibility, and acceptability will be conducted by the focus group, and this information will be processed and objectified using a thematic analysis devised by Braun and Clarke [11].

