### Statistical Analysis

Quantitative data will be analyzed using IBM SPSS Statistics (version 26.0). Descriptive statistics will be used to summarize categorical data (frequencies and percentages) and continuous variables (means and SD or medians and IQRs, depending on the distribution). Normality will be assessed using the Shapiro-Wilk test. Group comparisons will be made using *t* tests, ANOVA, Mann-Whitney *U*, or chi-square tests where appropriate. For repeated measures, linear mixed models or repeated measures ANOVA will be used. Qualitative data from focus groups will be coded and thematically analyzed following Braun and Clarke’s [11] approach.

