### Ethical Considerations

This study involves human participants and has been approved by Medical Research Ethics Committees United (reference number W24.065). Written informed consent to participate will be obtained from all participants prior to inclusion in the study.

All data collected will be pseudonymized before analysis to protect participants’ privacy. Personal identifiers will be replaced with unique study codes, and the key linking codes to participant identities will be stored separately in a secure, access-restricted location. Only authorized study personnel will have access to this information.

Participants will not receive any financial compensation or other incentives for participation in this study. Participation is voluntary, and participants may withdraw at any time without any consequences for their care.

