## Results

Staff training was completed in October 2024, and full implementation is ongoing. Up to 150 participants intend to be enrolled in the study. Preliminary findings, including data on usability and workload, are expected by July 2025 (see details in Table 2).

**Table 2 table2:** Measurement timetable for psychometric properties.

Objective	Instrument	0^a^	1	2	3	4 (evaluation/validation)	5	6	7	8 (evaluation/validation)
Fidelity	SUS^b^						Q^c^			Q
Acceptance	SC^d^/day				AD^e^					AD
Acceptance	SC/patient				AD					AD
Acceptance	IWS^f^	Q			Q		Q	Q	Q	Q
Adoption	EBPAS^g^	Q			Q				Q	Q
Appropriateness	SNR^h^									AD
Appropriateness	ADE^i^									AD
Feasibility	Thematic analysis				FG^j^			FG		FG
Time efficiency	Time measurement		M^k^	M	M		M	M	M	M
Predictive accuracy	MEWS^l^ and CREWS^m^		M	M	M	AD and M	AD (and M)	AD (and M)	AD	AD

^a^Numbers 0-8 represent the study months, starting from baseline (month 0) through to month 8.

^b^SUS: System Usability Scale.

^c^Q: questionnaire.

^d^SC: spot check.

^e^AD: administered data.

^f^IWS: Integrated Workload Scale.

^g^EBPAS: Evidence Based Practice Attitude Scale.

^h^SNR: signal-to-noise ratio.

^i^ADE: adverse device event.

^j^FG: focus group.

^k^M: manual measurement.

^l^MEWS: Modified Early Warning Score.

^m^CREWS: Continuous Remote Early Warning Score.

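### Table 1 gives the SUS independent-sample tests, although the schedule collects it twice on one ward and the protocol's own rule for repeated measures points elsewhere

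*Protocol article*

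**What the plan says.** - **Test.** In Table 1 (Methods, Implementation Phase), the SUS row names an "Unpaired *t* test or Mann-Whitney *U* test". Both are tests for two independent samples. The achievement criterion in that row is protocol adherence of at least 95%, not a SUS result.
- **Timing.** Table 2 (Results), titled "Measurement timetable for psychometric properties", has two questionnaire entries for the SUS. Its footnote reads "Numbers 0-8 represent the study months, starting from baseline (month 0) through to month 8", and counting columns puts the entries at months 5 and 8, the first and last months of phase 2.
- **Respondents.** The Outcomes section says "Approximately 70 nurses from the surgical ward will participate in the study and complete the IWS". SUS respondents are not described separately.
- **General rule.** The Statistical Analysis section says "For repeated measures, linear mixed models or repeated measures ANOVA will be used".
- **Companion questionnaire.** The Outcomes section uses the SUS and the Evidence-Based Practice Attitude Scale (EBPAS) together to measure adoption. Table 1 gives the EBPAS "Repeated measures ANOVA".
- **Coding.** Ethical Considerations says "Personal identifiers will be replaced with unique study codes", with a key kept separately.

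**The concern.** An unpaired test treats the month 5 and month 8 scores as coming from unrelated people. On one ward, three months apart, many respondents are likely to be the same, and a person's two usability ratings are likely to be positively correlated. The variance of the mean change is then smaller than the unpaired formula assumes, so the reported standard error is too large and the confidence interval too wide.

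What is at stake is sensitivity. A real change in perceived usability during phase 2 would more often fail to reach significance than it should. Usability is part of the stated primary objective, although the SUS itself is a secondary measure. The protocol also gives two incompatible instructions for the same data, one in the table and one in the text.

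**Working it through.** The protocol gives no sample size, SD, alpha, target difference or correlation for the SUS, so there is no figure to reproduce. The check has two parts.

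**1. Which contrast does the schedule support?** No SUS is collected before month 5, so phase 1 cannot be compared with phase 2. No separate respondent groups are defined for the SUS. Two time points in one ward's staff remain. Under the general rule quoted above, that is a repeated measure, and the EBPAS is already handled that way.

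**2. What does the unpaired test do to such data?**

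Inputs:
- n = 70 answering both times (assumed; the protocol's figure of about 70 belongs to the Integrated Workload Scale, IWS)
- SD = 15 SUS points (assumed)
- two-sided alpha 0.05 (assumed)
- within-person correlation ρ = 0.3 to 0.7 (assumed)
- a change of 5 points (assumed)

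Formulas:
- SE used by the unpaired test: SD·√(2/n) = 15·√(2/70) = 2.54
- True SE of the mean change: SD·√(2(1−ρ)/n). At ρ = 0.5 this is 15·√(1/70) = 1.79
- Overstatement of the SE: 1/√(1−ρ), which depends on neither n nor SD
- True size: 2·[1 − Φ(1.96/√(1−ρ))]
- Unpaired power at 5 points: Φ((5 − 1.96·2.54)/true SE)
- Paired power at 5 points: Φ(5/true SE − 1.96)

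| ρ | SE overstated by | True size, unpaired | Unpaired power, 5 points | Paired power, 5 points |
|---|---|---|---|---|
| 0.3 | 1.20 | 0.019 | 51% | 65% |
| 0.5 | 1.41 | 0.006 | 51% | 80% |
| 0.7 | 1.83 | 0.0003 | 51% | 95% |

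Unpaired power stays near 51% because the test's critical difference (1.96 × 2.54 ≈ 4.97 points) almost equals the assumed change.

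Simulation with 70 pairs (20,000 runs) gave t-test sizes of 0.019, 0.006 and 0.0005. The Mann-Whitney test (4,000 runs) gave 0.022, 0.008 and 0.0005, so the rank alternative does not help. The paired t test held its size at about 0.05.

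**Partial overlap.** If a fraction w of respondents answers both times, the true variance is 2·SD²(1 − wρ)/n. At ρ = 0.5:
- w = 0.8: √(1 − 0.4) = 0.775, and the size is 0.011 (simulated 0.011)
- w = 0.5: √(1 − 0.25) = 0.866, and the size is 0.024 (simulated 0.023)

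**Fewer respondents.** With n = 15 the simulated sizes are 0.022, 0.008 and 0.001 for ρ = 0.3, 0.5 and 0.7, so the distortion of size does not depend on 70 people replying.

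**The case against.** **The respondents and the contrast are not stated.** A reader might infer that the protocol gives the SUS to the same staff twice and compares those scores. It does not say so. An unpaired test would be valid for nurses against physicians, and physicians do take part in the focus groups. This stands as a limit on certainty. But no such SUS comparison is described, and the two scheduled time points are the only structure on offer. Complete overlap is not needed for the problem to arise, though its size shrinks as overlap falls.

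**The harm can be overstated.** A reader might infer that a wrong standard error means false claims of change. With positive correlation the error runs the other way. Nor would a real change simply be missed: 51% power means that a 5-point change is found about half the time under these assumptions. No stated success criterion turns on the SUS test.

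**The remedy is already in the text.** The general rule for repeated measures covers the SUS if it is read as one. This is fair, and it makes the point a conflict to settle rather than a plan without a valid method. The table, however, is the more specific instruction, and an analyst would probably follow it.

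**Linkage is not assured.** The coding statement is general and does not say that SUS forms carry a staff code. This stands, so a paired analysis is conditional on linkage. The repeated measures plan for the EBPAS makes it likely that linkage is intended.

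**Conclusion.** The point holds as an inconsistency between Table 1 and the protocol's own repeated-measures rule. On the contrast that the schedule supports, following the table cell gives too large a standard error: 1.20 to 1.83 times too large for correlations 0.3 to 0.7 with full overlap. The result is a conservative test with reduced power.

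The numerical size rests on assumed values for SD, correlation, respondents and change, and on inferred overlap of staff. The direction needs only some overlap and a positive correlation. The IWS, which is the primary outcome, is not affected. The change should be made, but the study's main conclusion does not depend on it.

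**What to change.** - Replace the test in the SUS row of Table 1 with the linear mixed model already allowed in the Statistical Analysis section: month as fixed effect and a random staff intercept. This keeps staff who answer only once. A paired t test or Wilcoxon signed-rank test on staff with both scores is a simpler alternative.
- State who completes the SUS and that the contrast is month 8 against month 5. Report the mean change with a 95% confidence interval.
- Carry the staff study code on the SUS forms at both months so that responses can be linked. If they cannot be linked, state this and note that the unpaired test is conservative.

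The cost is one table cell, a sentence or two of text and a code on the forms. No extra questionnaires are needed. If month 5 forms were already collected without a code, only the last option remains for those responses.

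### The only success rule for the primary outcome counts device users and contains no workload quantity, so acceptance could be declared while IWS workload rises

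*Protocol article*

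**What the plan says.** The Outcomes section states: "The primary outcome will be acceptability, specifically evaluating workload as measured by the Integrated Workload Scale (IWS". It describes the scale as "ranging from “not demanding” to “work too demanding” on a 9-point Likert scale", so a higher rating means heavier workload. It adds: "Approximately 70 nurses from the surgical ward will participate in the study and complete the IWS". Table 2 schedules the IWS questionnaire at months 0, 3, 5, 6, 7 and 8.

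Table 1 (Implementation Phase) lists three instruments under Acceptance: spot checks per day, spot checks per patient, and the IWS, the last with a 1-way ANOVA. The achievement criterion on all three rows is "Acceptance achieved when ≥75% of nurses use the device regularly". The adoption criterion, on the row for the Evidence-Based Practice Attitude Scale, is device use above 70% by clinical staff.

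The Fidelity row names the SUS as its instrument and gives the criterion "Fidelity achieved when protocol adherence is ≥95" (a percentage). The Outcomes section assigns the SUS to adoption.

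**The concern.** An achievement criterion turns data into a stated conclusion. For the primary outcome, the data are workload ratings and the criterion is a head count of device users. The two can move in opposite directions: nurses may use the device regularly and find the work more demanding. In that case the plan's rule returns success on an outcome that the plan itself defines as workload. The Discussion anticipates lower perceived workload, so a reader told that acceptance was achieved would naturally take it as support for that expectation.

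The Fidelity row has a milder form of the same problem: its criterion is not a quantity that its listed instrument measures.

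**Working it through.** **1. Is there an IWS success rule anywhere in the article?**

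| Place | What it gives | IWS threshold or direction for success? |
|---|---|---|
| Outcomes | IWS workload as primary outcome | No |
| Table 1, Acceptance | at least 75% of nurses using the device | No |
| Table 1, Time efficiency | at least 20% less monitoring time | No; separate objective, measured time |
| Statistical Analysis | general list of tests | No |
| Discussion | anticipates a reduction, no size | Expectation only, not a rule |

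The 75% figure is a declared cut-off without inputs, so there is no derivation to reproduce.

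**2. What the rule requires.** Input: about 70 nurses (Outcomes). 0.75 × 70 = 52.5, so 53 users are needed: 53/70 = 75.7% passes and 52/70 = 74.3% fails.

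**3. How often it is met.** Let p be the true share of regular users. The article gives no expected share, so p is assumed, with nurses independent. P(met) = P(X ≥ 53), X ~ Binomial(70, p):

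| p | 70% | 75% | 80% | 85% | 90% or more |
|---|---|---|---|---|---|
| P(met) | 0.18 | 0.51 | 0.85 | 0.987 | >0.999 |

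The IWS does not appear in this calculation. At a given p the probabilities are the same whether workload falls, stays level or rises.

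**4. Illustration of both events together.** Assumptions, none from the article: 70 independent ratings per phase, two-sided 5% test, device use independent of IWS, a true IWS rise of δ points with standard deviation σ. The probability of detecting the rise is about Φ(δ / (σ√(2/70)) − 1.96), and the joint probability multiplies this by P(met). For δ = 1 and σ = 1.5: σ√(2/70) = 0.2535, 1/0.2535 = 3.94, and Φ(3.94 − 1.96) = 0.976.

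| δ | σ | P(significant rise) | Joint, p = 95% | Joint, p = 80% |
|---|---|---|---|---|
| 1.0 | 1.5 | 0.976 | 0.976 | 0.832 |
| 1.0 | 2.0 | 0.841 | 0.841 | 0.716 |
| 0.5 | 1.5 | 0.505 | 0.505 | 0.430 |
| 0.5 | 2.0 | 0.315 | 0.315 | 0.269 |

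These are scenarios, not predictions. The same nurses rate repeatedly, so independence is a simplification. The table shows only that the use rule does nothing to prevent the two results from occurring together.

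**5. Overlap with adoption.** If the adoption criterion were applied to the same 70 nurses (an assumption; the article says clinical staff), use above 70% means more than 49, so at least 50 (50/70 = 71.4%). Acceptance needs 53. On that reading the primary and a secondary objective differ by three nurses on the same measure.

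**6. Fidelity.** Tables 1 and 2 both list the SUS as the only fidelity instrument, so a misread table row is unlikely to explain it. A usability score gives no adherence percentage.

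**The case against.** The strongest reply is that the IWS is analysed in its own right. It is named as primary, measured on six occasions and given its own test, and nothing says that the Table 1 criterion replaces that analysis. This stands: a rise in workload could be seen and reported. It would not, however, change whether acceptance counts as achieved.

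A second reply is that the criterion may be one merged cell covering all three Acceptance rows. The adoption text on the signal-to-noise row suggests that cells were filled downward. This also stands, and it means that the IWS need not be expected to produce the 75% figure. But the merged cell would still be the only Acceptance criterion, and it would still omit workload.

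A third reply is that a condensed article may leave detail to the full protocol. That partly answers the fidelity point, since the source of the adherence figure may be given there. It does not answer the main point, because the article does state a success rule and states one that does not fit the outcome.

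Two stronger readings are tempting, and the article does not support them.

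- A reader might infer that the 75% is met almost automatically, because in phase 2 "the wearable will become the primary tool for patient monitoring, supplemented by manual spot checks by nurses as needed". But spot checks remain, patients may decline, regular use is undefined and no use rate is given. At a true share of 70% to 75% the rule is met with probability only 0.18 to 0.51.
- A reader might infer from the thematic-analysis entry that the criterion "Feasibility achieved when 80% of clinicians can successfully implement the device" would be judged on the 15 focus-group volunteers. The Outcomes section assesses feasibility among health care employees generally and adds timed checks. No denominator of 15 is stated for the 80%.

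**Conclusion.** The main point holds. The primary outcome is IWS workload, and its only achievement criterion is a device-use percentage with no workload content. Acceptance can be declared at 53 of 70 nurses with IWS ratings lower, unchanged or higher. This follows from the text alone and does not rest on the assumed use rates or standard deviations. It is a wrongly stated decision rule, not missing detail.

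The conclusion is limited to the declared result. It does not extend to saying that the IWS goes unanalysed, that use is secured by ward policy, or that feasibility rests on 15 people. The SUS entry under Fidelity is a lesser inconsistency between Table 1 and the Outcomes section.

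**What to change.** **Acceptance.** Replace the criterion with one on the IWS: the difference between phase 2 (months 5 to 8) and the pre-implementation ratings (months 0 and 3), with its 95% CI. Claim a workload reduction only if the whole interval lies below 0. Claim no worsening only if it lies below a stated margin. The Statistical Analysis section already provides linear mixed models for repeated measures, which can supply this contrast.

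**Adoption.** Treat the share of nurses using the device as an adoption measure, and reconcile 75% of nurses with 70% of clinical staff into one threshold, with one denominator and a definition of regular use. Moving the 75% across without this would leave two use thresholds for one objective.

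**Fidelity.** Compute adherence from the stored device and EHR records, and report the SUS as usability, in line with the Outcomes section.

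**Cost.** No new IWS collection is needed, since the ratings are already scheduled. The primary criterion can now be missed. The article gives no basis for a margin and reports implementation as under way, so the margin must be justified, dated and fixed before anyone examines the IWS data. If that is no longer possible, only the comparison with 0 avoids a margin chosen with the data in view, and the date of the change should be reported.
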